### Randomization, allocation

The block randomization, stratified by trial centers, is performed using a randomization list from a centralized secure online server (internet) 24/7. A backup solution with sealed opaque envelopes will be available in each vehicle participating in the study for situations that do not allow access to the secure randomization server (off-grid area, connection difficulty). There is a stratification of the draw at each center in a 1:1:1:1 distribution: (A + C) 2 min blind, (A + D) 2 min with guidance, (B + C) 4 min blind, and (B + D) 4 min with guidance (Fig. 1).

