### Trial interventions

CA, matching the eligible criteria, managed by an out-of-hospital resuscitation team can be included according to a procedure of immediate vital emergency (article L1122-1-3 of the Code of Public Health) [27]. The randomization is performed by the out-of-hospital resuscitation team’s doctor during the transportation on the spot to know the randomization arm before the arrival at the place of the intervention. The patient is randomized using the online centralized 24/7 server or the backup sealed opaque “off-grid area” emergency randomization envelopes as described in the “Randomization, allocation” section above.

For all groups, the CPRmeter^®^ CC guidance system was positioned on the patient’s chest with a disposable adhesive. The CPRmeter^®^ is always on for all groups. (1) In the CC guidance situation by the CPRmeter^®^ (group D), rescuers have onscreen real-time visual feedback on the quality of the CC performed and indications of corrections to improve the quality, if necessary. (2) In cases of nonguidance of the CC by the CPRmeter^®^ (blind), a specific screen cap is set up on the screen to hide the feedback in the unguided group (group C). The CPRmeter^®^ is always on to record the CC quality data.

The duration or rhythm of a relay is the time during which a rescuer performs a CC before being relayed by another rescuer. This time is 2 min in group A according to the guidelines in effect and 4 min in group B, which is the experimental group.

The CPR of OHCA is therefore normally undertaken according to the guidelines in effect by the out-of-hospital resuscitation team, except for the relay rhythm in group B, which is 4 min. Due to the 2 × 2 factorial design, four situations are possible (Fig. 1):
CC unguided + relay between 2 rescuers switching at 2 min (C + A)CC unguided + relay between 2 rescuers switching at 4 min (C + B)CC guided + relay between 2 rescuers switching at 2 min (D + A)CC guided + relay between 2 rescuers switching at 4 min (D + B)

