### Data collection

Data will be collected using international Utstein-style guidelines on reports for OHCA and using the automatic data registration of the CPRmeter^®^ device. Data from the CPRmeter^®^ will be uploaded to the section of the French national network of the RéAC Cardiac Arrest Registry (http://www.registreac.org/) dedicated to the study. All other data will be collected by doctors in charge of the patient and entered into an eCRF of the dedicated section of the RéAC Cardiac Arrest Registry. Clinical research assistants (locally and in the promoting center) will help and monitor the data collection and the eCRF. The data input is checked by computer.

Apart from the CC quality data report by the CPRmeter^®^, data collection will be performed as follows:

#### At day 0

Demographic characteristics: identity, social security number, intervention, street address, age (year), sex (male/female), weight (estimated, in kilograms), height (estimated, in meters)Patient history: medical history (cardiovascular, respiratory, diabetes, end of life, others)History of the disease: presumed etiology of CA (cardiac, neurological, respiratory, asphyxiation, poisoning, drowning, unknown, others), durations of no-flow and low-flow periods before medical resuscitation (minutes), existence of witnesses, resuscitation maneuvers undertaken before the arrival of professional rescuers (CC, defibrillation, ventilation)History of the advanced CPR carried out by the out-of-hospital resuscitation team:
Duration of low-flow, no-flow, and advanced resuscitation (minutes, obtained by CPRmeter^®^ recording)Quality of the CC and its components (frequency in CC per minute, depth in millimeters, and release in grams obtained by the CPRmeter^®^ recording)EtCO_2_ values (mmHg) 1 min (± 20 s) after intubation, the highest obtained during CC (before ROSC) and at the end of resuscitation (1 min ± 20 s after the ROSC or during the decision to end resuscitation) [32, 33]External electrical shocks (number, intensity in joules)Initial rhythm upon the out-of-hospital resuscitation team arrival (asystole, ventricular fibrillation, ventricular tachycardia without pulse, electromechanical dissociation)Numbers and total doses of vasopressor amines and antiarrhythmic administration (milligrams)ROSC or death

Survival at hospital admission

#### At hospital discharge or at day 30

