### Statistical analyses

The main analysis population will be defined as all randomized patients for whom CPR has been engaged, according to a modified intent-to-treat principle. Randomized patients who do not fulfill the inclusion criteria, die, or have a ROSC at prehospital team arrival will be excluded from the main modified intent-to-treat principle analysis. We plan to conduct a pure intent-to-treat analysis in which these excluded patients and patients with missing data will have their outcome imputed by multiple imputation process. This analysis will test the effect of these exclusions on trial outcomes. The statistical analysis plan will follow the recommendations of the tests with a factorial plan described in the CONSORT statement [35], namely, (i) the verification of the absence of interaction between the 2 interventions tested (here on different criteria of judgment) and (ii) a separate analysis by type of multivariate intervention that will systematically include the effect of the untested intervention. Regarding the main criterion of judgment, the average percentage of CCF for comparison of A versus B and the average percentage of CCS for comparison C versus D, the two groups will be compared in terms of superiority of the 4-min group (B) and the guidance group (D) by a multivariate generalized linear regression model including the randomization group as an explanatory variable as well as the other intervention received as a covariable of the model and possibly the interaction of the 2 interventions if it is significant (Student’s test for independent series).

The other criterion (secondary outcomes) will be compared between the groups using the appropriate tests and in an exploratory manner. For example, the qualitative variables will be compared between the groups with the *χ*^2^ test, the quantitative variables by Student’s *t* test, and the survival by the log-rank test.

All confidence intervals of the parameters to be estimated will be established at 5% risk (95% confidence interval). No interim analysis will be performed for primary outcomes (CCF and CCS). The significance level is set at 0.05. The analysis will be performed in SAS software v9.4 (SAS Institute NC, Cary).

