### Determination of sample size

We estimated the calculation of the number of subjects required in this trial using a factorial design for the comparison of 2 min versus 4 min (A vs B) on the average percentage of CCS.

With an average CCF of 70% [36] in the control group (group A, 2 min) and a 5% improvement in the experimental group (group B, 4 min), a power of 90%, a two-tailed alpha risk of 5% bilateral, and a standard deviation of ± 17%, 243 subjects per group are required to compare the effect of 2 min versus 4 min (A vs B) on the average percentage of CCF.

Regarding the guiding hypothesis, with a difference of 15% in the CCS between the guided group (D) and the blinded group (C), a standard deviation of ± 36% (12), alpha 5%, and beta 10%, the number of subjects needed is lower (122 per group).

We plan to include 500 patients according to the sample size needed for hypothesis A vs B (243 per group), which is higher than that needed for hypothesis C vs D (122 per group).

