## Discussion

The study will contribute to the field of literature on the impact of real-time feedback on CC quality in practical conditions of OHCA resuscitation. No definitive position on the benefit of real-time feedback on CC quality has been assessed [9, 20]. This topic is complicated and has many possible confounding factors and biases. A definitive answer will probably come from a meta-analysis or a large-scale study. It seems to us that this study can be one of the small steps toward a conclusion.

The study will also provide insight into the feasibility of extending the switch time duration between two rescuers from the currently recommended 2 to 4 min. Beyond feasibility, it will provide clues on the effect of an extension of the switch time on the CC quality. With the two groups, guided and blinded to real-time feedback, it will also determine whether an extension of the switch time provides a CC quality as efficient as the current 2 min regardless of real-time feedback, only with real-time feedback or whether CC quality decays even with real-time feedback. Even if the extension of the switch time does not have a positive effect on CC quality, we will have concrete data on its effect on the chest compression fraction time. Since this has been highlighted as a determining element of the quality of resuscitation, it will provide an interesting perspective for future research and care in CA. As an anticipated limitation, we know that the sample size—designed to answer our questions—will probably be insufficient to provide significant data on mortality and morbidity. However, we believe this study may help provide a clearer view of some important aspects of the management of OHCA and may open new opportunities for further research.

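### Both primary models name no baseline covariate; prespecifying a few already collected could modestly narrow the intervals, mainly to the benefit of the CCF comparison

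*Protocol article*

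**What the plan says.** Under Statistical analyses, the protocol article compares mean CCF between the 2-min and 4-min relay groups, and mean CCS between the blind and guided groups. The regression for each is described as "including the randomization group as an explanatory variable as well as the other intervention received as a covariable of the model". One further term, the product of the two factors, enters only when it reaches significance. No other term is named. The word multivariate in that section refers to carrying the other randomised factor in the model.

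Under Data collection (At day 0), the items recorded include "age (year), sex (male/female), weight (estimated, in kilograms), height (estimated, in meters") and "Initial rhythm upon the out-of-hospital resuscitation team arrival".

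Under Trial interventions, randomisation takes place "during the transportation on the spot to know the randomization arm before the arrival at the place of the intervention". Rhythm and weight are therefore recorded after allocation. The rhythm found on arrival nevertheless precedes any compression given under the protocol.

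Under Determination of sample size, the relay comparison is planned thus: "With an average CCF of 70% [36] in the control group (group A, 2 min) and a 5% improvement in the experimental group". It assumes SD 17, two-sided alpha 5% and power 90%, giving 243 per group. The guidance comparison assumes a 15-point CCS difference and SD 36, giving 122 per group. The planned total is 500.

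**The concern.** Neither relay length nor feedback can change a patient's age, sex, body size or rhythm on arrival. If such variables predict the outcome, including them in a linear model moves explained variance out of the error term and tightens the estimated effect.

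A link is plausible for both outcomes. CCF is compression time divided by CPR time, so pauses for shocks in patients with a shockable rhythm would lower it. CCS requires correct depth and release, which may vary with body size, age and sex. The document states neither relationship.

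Any benefit falls mainly on the relay comparison, which sets the sample size: 2 × 243 = 486 of the 500 planned patients, a margin of 14. Naming covariates in advance would also remove the temptation to choose adjustments later if rhythm happened to be unbalanced between arms.

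**Working it through.** **Inputs from Determination of sample size.** CCF: difference 5 points (70% to 75%), SD 17. CCS: difference 15 points, SD 36. Two-sided alpha 5%, power 90%. With 500 patients allocated 1:1:1:1, each level of each factor has 250.

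**Step 1: reproduce the plan's figures.** n per group = 2 × (1.960 + 1.2816)² × SD² / d².
- CCF: 2 × 10.508 × 289 / 25 = 242.9, so 243. This matches.
- CCS: 2 × 10.508 × 1296 / 225 = 121.1, so 122. This matches.

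The sample size is thus an unadjusted two-mean calculation that counts on no gain from covariates.

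**Step 2: power at 250 per group without patient covariates.** Standard error = SD × √(2/250); power = Φ(d/SE − 1.96).
- CCF: SE = 17 × 0.08944 = 1.52; 5/1.52 = 3.29; power 90.8%.
- CCS: SE = 36 × 0.08944 = 3.22; 15/3.22 = 4.66; power 99.7%.

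**Step 3: add covariates.** The residual SD becomes SD × √(1 − R²). R² is an assumption, shown as a range. Half-widths are 1.96 × SE, in points.

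| Assumed R² | CCF n per group for 90% | CCF power at 250 | CCF half-width | CCS power at 250 | CCS half-width |
|---|---|---|---|---|---|
| 0 | 243 | 90.8% | 2.98 | 99.7% | 6.31 |
| 2% | 239 | 91.3% | 2.95 | 99.7% | 6.25 |
| 5% | 231 | 92.1% | 2.90 | 99.8% | 6.15 |
| 10% | 219 | 93.4% | 2.83 | 99.8% | 5.99 |
| 20% | 195 | 95.7% | 2.67 | 99.9% | 5.64 |

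The relative narrowing is the same for both outcomes: √0.90 = 0.949, about 5%, at R² of 10%, and √0.80 = 0.894, about 11%, at 20%.

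**Step 4: what R² might initial rhythm alone supply?** For a binary covariate with prevalence q and outcome difference Δ, R² = q(1 − q)Δ²/SD². Both q and Δ are assumptions.
- Δ = 10 CCF points: 0.1275 × 100/289 = 4.4% at q = 15%; 0.2275 × 100/289 = 7.9% at q = 35%.
- Δ = 5 points: 1.1% and 2.0%.

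**Step 5: cost in degrees of freedom.** Six extra parameters, more than the four proposed, would inflate the residual variance by about 497/491 = 1.012 if they explained nothing. Break-even is at R² of about 6/497 = 1.2%. A noncentral t calculation with these degrees of freedom charged gives CCF power of 91.2%, 92.0%, 93.3% and 95.6% at R² of 2%, 5%, 10% and 20%, about 0.1 point below the table.

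**Step 6: fewer analysed patients.** If exclusions left 225 per group, CCF power would be 87.7% without covariates and 90.8% at R² of 10%. At 200 per group the figures are 83.7% and 87.3%.

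**The case against.** The strongest reply is that nothing here is wrong. Comparing randomised groups without patient covariates is valid, chance imbalance is already allowed for in the type I error, and the sample size was computed on that basis. All of this stands. A reader might infer from the concern that the primary analysis is biased or the trial undersized; the document supports neither.

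It is also fair to say that an analysis plan not shown may add covariates, and that the wording of the model does not expressly rule them out. However, the article does name the model's terms and a specific covariable, so the suggestion addresses a stated method.

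A second tempting reading is that precision is certainly being lost. It may not be. CCF and CCS largely measure rescuer performance, and patient factors may explain little; at R² of 2% the gain in CCF power is half a point. Nor is adjustment free. Weight is an estimate, and rhythm and weight are recorded after allocation by staff who know the arm.

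A third is that the secondary tests should be replaced by adjusted regressions. The article calls those comparisons exploratory, offers its tests only as examples, and concedes that the sample "will probably be insufficient to provide significant data on mortality and morbidity". That leaves no fixed method to correct.

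Two neighbouring matters should not be borrowed as support. Losses through post-randomisation exclusion are a separate problem that covariates offset only in part (Step 6). Centre, the stratification factor ("The block randomization, stratified by trial centers, is performed using a randomization list"), is also absent from the named model. It has a better-grounded claim to inclusion, but on its own account.

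**Conclusion.** The point holds as an optional efficiency improvement. The named primary models contain the two randomised factors and possibly their interaction, while four usable baseline variables are already collected.

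For CCF the gain in power at 250 per group is about 0.5, 1.3, 2.6 or 4.9 percentage points at assumed R² of 2%, 5%, 10% or 20%. The document cannot show which value applies. For CCS the gain in power is at most 0.3 points, so interval width is the only practical benefit.

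These figures assume a 5-point CCF effect with SD 17, a 15-point CCS effect with SD 36, all 500 patients analysed, and a linear covariate effect.

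**What to change.** In Statistical analyses, add one sentence before unblinding: both primary models, in the modified intent-to-treat population, also include initial rhythm (shockable or not), age, sex and estimated weight, and the result without these covariates is reported as supportive. Because the Blinding section concedes that the relay arm can be read from the recorded data, the set is best fixed before analysts see outcome data.

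Two details need a rule. Missing covariate values should be handled consistently with the multiple imputation already planned. In the pure intent-to-treat analysis, patients with ROSC at team arrival have no natural value for initial rhythm, so the text must say how they enter or that the term is omitted there.

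The cost is a change of wording. No extra patients or data items are needed, and if the covariates prove uninformative the loss of precision is negligible (Step 5).

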The outcome of out-of-hospital cardiac arrest (OHCA) is significantly, positively, and independently correlated with the suitability for different CCF targets, CC frequency, CC depth, and brief predefibrillation pause (< 10 s) [17, 18]. Mechanical CC devices have not proven their superiority over manual CC [19], and manual CC remains the gold standard. There is evidence that CC guidance improves adequacy to recommendations and allows closer alignment with the CC frequency, depth, and release objectives [20]. We have demonstrated in simulation that the guidance of the CC delays the deterioration of the overall quality of the CC and its components (frequency, depth, and release) related to fatigue during an extended CC beyond the 2-min CC relay currently recommended [21].

Strategies to better match the recommendations regarding the quality of the CC associated with an improvement in CC should add or even enhance their beneficial effects for the management of CA. Achieving high-quality CPR requires the measurement of the CPR quality (CC and CCF) [22, 23].

This idea of a strategy of support enhanced by the “bundle” of concepts is developing in the literature. Thus, Cheskes et al. [24] describe a “high-quality CPR” such as the combination of a CCF greater than 70% and reaching the objectives in the recommendations for frequency and depth of CC.

The use of tools guiding CC quality still needs to be specified. Indeed, studies on their use in real-life situations are criticized for their methodological qualities and their sample sizes [25]. The use of a real-time guidance tool is proposed as an option in the latest recommendations without being mandatory due to a lack of current evidence [9]. Its use or nonuse does not imply any obvious loss of success for the patients. Evidence of its usefulness therefore remains to be sought.

For this reason, we want to perform an original, randomized, multicenter study to provide some answers to questions about the possibility of improving CCF by lengthening the time between two CC relays and the effect of guidance on the quality of the CC.

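### A data-driven rule decides whether the interaction enters the primary model, and the contrast then tested is not fixed, so the stated 5% error and 90% power need not hold

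*Protocol article*

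**What the plan says.** The Statistical analyses section sets out two steps. The first is "the verification of the absence of interaction between the 2 interventions tested". The second is a separate regression for each primary outcome (CCF for 2 min against 4 min, CCS for blind against guided). That model holds the randomisation group, "the other intervention received as a covariable of the model", and "possibly the interaction of the 2 interventions if it is significant". No separate level is given for the interaction test; the section says only "The significance level is set at 0.05". It names neither a factor coding nor the contrast that carries the primary conclusion when the interaction term is in the model.

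The Determination of sample size section treats each question as a plain two-group comparison of margins. For CCF it assumes "a 5% improvement in the experimental group (group B, 4 min), a power of 90"%, with "a two-tailed alpha risk of 5% bilateral, and a standard deviation of ± 17"%, and reaches 243 per group. For CCS it assumes a 15-point difference and an SD of 36, and reaches 122 per group. The plan is to include 500 patients. Neither calculation allows for an interaction or for a preliminary test.

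**The concern.** In a 2 × 2 trial, a model without an interaction term gives one effect per factor, the marginal effect on which this trial is sized. A model with the term gives several candidates: the effect averaged over the other factor, and a simple effect at each of its two levels. Under ordinary 0/1 coding, the coefficient on treatment turns from the marginal effect into the simple effect at the reference level, which rests on half the patients. A rule that moves between models according to a significance test can therefore change what is estimated as well as how precisely. Both primary comparisons are governed by this one sentence.

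The check is also asked to do something it cannot do. A non-significant interaction test does not verify absence unless the test has good power against interactions of a size that matters.

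Finally, the sentence uses the randomised group for the factor under test but the intervention *received* for the covariable. Taken literally, that would adjust for something determined after randomisation.

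**Working it through.** **Inputs.** CCF: difference 5, SD 17. CCS: difference 15, SD 36. Two-sided 5%, power 90%, total 500 (all from Determination of sample size). Allocation is 1:1:1:1 (Randomization, allocation), so 250 per margin and 125 per cell. Assumed here: the interaction is tested at two-sided 5%, cells are equal, outcomes are normal, and no patients are lost to the modified intent-to-treat exclusions.

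**The plan's own figures.** n per group = 2 × [SD × (1.96 + 1.2816) / difference]².
- CCF: 2 × (17 × 3.2416 / 5)² = 242.9, so 243. Reproduced.
- CCS: 2 × (36 × 3.2416 / 15)² = 121.05, so 122. Reproduced.

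**Standard errors for CCF at 500 patients.**
- Marginal effect: 17 × √(4/500) = 1.52. Power for 5 points: Φ(5/1.52 − 1.96) = 91%.
- Simple effect, 125 against 125: 17 × √(2/125) = 2.15. Power for 5 points: Φ(5/2.15 − 1.96) = 64%.
- Interaction (difference between the two simple effects): 17 × √(16/500) = 3.04. Power for 5 points: Φ(5/3.04 − 1.96) = 38%. Size detectable with 80% power: (1.96 + 0.84) × 3.04 = 8.5 points.

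The preliminary test would thus miss an interaction as large as the CCF design effect in about 62% of trials.

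**The two-stage rule, reference-coded reading.** Each simulated trial tests the interaction. If it is significant, the treatment test is the simple effect at the reference level; otherwise it is the main-effects estimate. There were 1 to 2 million runs per scenario.

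| Scenario | Interaction significant | Two-stage rule rejects | Main-effects model rejects |
|---|---|---|---|
| No effects at all | 5% | 6.4% (about 8% if either simple effect may count) | 5.0% |
| CCF 5 at both levels | 5% | 89% | 91% |
| CCF 2.5 at reference, 7.5 at other | 37% | 58% | 91% |
| CCF 7.5 at reference, 2.5 at other | 38% | 94% | 91% |
| CCS 15 at both levels | 5% | 98.0% | 99.7% |
| CCS 7.5 at reference, 22.5 at other | 64% | about 48% | 99.7% |
| CCS 22.5 at reference, 7.5 at other | 64% | 99.9% | 99.7% |

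With an average CCF effect of 5 and an interaction of 5, the reported 95% interval covers the average effect in about 80% of trials, whichever level is the reference.

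**The two-stage rule, averaged-effect reading.** With −1/+1 coding in balanced or near-balanced cells (40,000 full regressions per scenario), type I error is 4.9% to 5.1%. CCF power is 90.6% without an interaction and 90.3% with simple effects of 2.5 and 7.5. Adding the term barely moves the estimate, and the design figures hold.

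**The case against.** The strongest reply is that the documents point to the averaged contrast. The Primary outcomes section aggregates CCF by A vs B and CCS by C vs D, and the trial objectives are put in the same terms. Neither a simple effect nor reference coding is mentioned. On that reading the stated error and power survive, and coding details are commonly left to an analysis plan that is not shown here. This largely stands, and it limits the point to *need not hold*. It does not remove the point: the conditional rule is in the published text, and nothing there fixes the contrast after a significant interaction.

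Several stronger readings are tempting and are not supported.

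- **The rule always costs power.** It does not. Without a true interaction the CCF loss is about 2 points. With one, power may fall or rise according to the reference level.
- **Type I error can reach 20%.** With a zero average CCF effect and simple effects of +2.5 and −2.5, the reference-coded rule rejects in 20% of trials. Those simple effects are truly non-zero, so this is not a type I error for a simple effect. It shows only that the rejection no longer answers the marginal question.
- **The trial expects an interaction on CCF.** The Background reports from simulation that "guidance of the CC delays the deterioration of the overall quality of the CC". That concerns compression quality, the domain of CCS. For CCF, the document mentions only a possible combined effect.
- **The analysis adjusts for treatment actually given.** The population is modified intent-to-treat and no as-treated grouping is defined, so *received* may be no more than loose wording.

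**Conclusion.** The concern holds in conditional form. The text lets a test on the same data choose the primary model and leaves the subsequent primary contrast open, while the trial is sized on the margins alone. How much this matters depends on a choice the document does not make. With the averaged effect in near-balanced cells, nothing material is lost. With the reference-coded coefficient, type I error under the complete null rises from 5% to about 6.4%, and under a true interaction as large as the design effect the reference level alone moves power by 36 points for CCF (58% to 94%) and about 52 points for CCS (48% to 99.9%). The large shifts require a true interaction, and all figures rest on equal cells of 125 and a 5% interaction test. Separately, and under either reading, a non-significant result cannot verify absence of interaction: power is 38% for a 5-point CCF interaction.

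**What to change.** In Statistical analyses:

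1. State that the primary analysis of each endpoint is the main-effects model, with relay and guidance both as randomised and no interaction term, whatever the interaction test shows.
2. Delete the condition that brings the interaction into that model when it is significant.
3. Always report, as prespecified secondary results, the interaction estimate with its 95% CI, the four cell means and the simple effects. Present these as an assessment of interaction rather than as verification that there is none.
4. Replace the intervention *received* by the intervention *randomised*.

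This changes wording only. On the assumptions above, type I error is 5.0% for each test and power at 500 patients is 91% for CCF and 99.7% for CCS, so the sample size stands. The small cost is that, with a strong interaction, the headline effect is an average over two differing effects, which the reported cell means make visible.
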